## STUDY IMPLEMENTATION

### Protocol

Individuals expressing interest were contacted via telephone or video conferencing to arrange a briefing. This meeting included screening for inclusion and exclusion criteria, a verbal overview of the study and an opportunity to ask questions. Participants were provided with an information sheet and re-contacted at least 7 days later when they were provided with a further opportunity to ask questions and then, if willing, were enrolled on the trial. Once enrolled, participants provided their written informed consent to participate in the study and were allocated an enrolment number. A secure third-party service (Study-Randomizer) randomised participants into intervention or control groups stratified by age and sex with recruitment logs to ensure randomisation in recruitment order.

Following randomisation, a study start date approximately one week later was agreed. This provided time for an activity tracker (Fitbit Charge 5) to be posted to those allocated to the intervention group. Subsequently, in an online meeting, a study team member aided participants in downloading the PaceMe app from the relevant app store, ensuring they successfully registered an account and proceeded through the onboarding and digital consent screens. The app then asked for further participant information, including an activity tracker number for those allocated to the intervention group. The tracker number acted as a 'switch' such that participants who did not provide one were taken to the control version of the app, in which the home screen consisted of each of the questionnaires only. For those who did provide a tracker number, their home screen was an enhanced version of the PaceMe app, which included live metrics of their activity pacing for that day and over the previous days (see below).

The intervention used live activity tracking to help people with long COVID to better manage their daily activities so as to reduce the risks of inducing a bout of PEM. To do this, the intervention group had their activity continually tracked using a wrist worn activity tracker (Charge 5, Fitbit, San Francisco, USA). However, the Fitbit phone app does not process activity data in a manner suitable for people at risk of PEM. Consequently, we removed or turned off all of the activity notifications from the Fitbit app and employed our own activity server to link each participant's activity data to their PaceME app. Our activity server accessed the tracker data every 3 minutes and collected the relevant activity data in 1-minute epochs for the current day (heart rate and steps). Once collected, our server processed this data and stored the results in a database that enabled live streaming of each user's data to the relevant part of the PaceME app. This meant each user was able to get personalised, live updates within the PaceME app, giving them an overview of their activity so far for the day along with an indication as to whether this amount of activity had occurred prior to a previous bout of PEM. Participants were free to use this information to better plan their day-to-day activities to avoid over-exertion.

During this process, a member of the research team ensured that all of the alerts, notifications and prompts which encouraged additional exercise, managed by the trackers own app had been switched off or removed. Both intervention and control participants also received automated alerts to remind them when they were due to complete specific questionnaires and reminders if they remained uncompleted a week after the intended completion time. In addition to the instruments, the app also enabled participants to log any issues with the app and register a call back request from the team in the event of any issues.

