### *Randomisation*

Participants will be randomised to one of the two trial arms using 1:1 allocation ratio. Randomisation will be performed by a web-based online randomisation system (Study Randomizer). We will randomise participants remotely and participant blinding is impossible given the nature of the intervention.

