### *Study procedure*

The intervention will be a randomised controlled trial (RCT) to determine if adaptive pacing (AP) using activity tracking and just-in-time support messages can improve symptom management of people with long-COVID. The trial will compare the symptom management of people allocated to usual care versus those receiving the intervention. The intervention will be provided via a bespoke support platform incorporating a wearable activity tracker (Fitbit Charge 5, Fitbit, USA), a data processing server, and a cross-platform (iOS and Android) mobile app (PaceMe). Participants will be recruited via online adverts and through long-COVID support groups. Those interested in taking part will undergo a screening interview for

eligibility and were subsequently randomised by a third party (studyrandomizer.com) into intervention or control arms of the trial balanced for gender.

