## **STATISTICAL CONSIDERATIONS AND DATA ANALYSIS**

### *Sample size and statistical power*

To determine sample size, our primary outcome variable is the DSQ-PEM. Using previous work, a minimum clinically relevant difference can be estimated as a change of 13 points on a 100-point scale . Assuming a standard deviation (SD) of 25 , this resulted in a pairwise effect size of  $d=0.5$  (Cohen’s  $f=0.25$ ). We calculated our desired sample size for a two-way mixed-model (within- and between-subjects) analysis of variance (ANOVA). Using the WebPower package in R Studio, and the `wp.rmanova` function, with two groups, two time points, a medium effect size ( $f=0.25$ ), assuming sphericity, an alpha of 0.05, desired statistical

power of 0.9, testing for an interaction effect, the total n was 170 (85 per group). Consequently, we aimed to recruit 125 participants per group to allow for 30% drop-out.

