### *Statistical methods*

All analyses will be conducted using Jamovi version 2.3.21. Data will be tested for normal distribution and homogeneity of variance to confirm parametric assumptions are met. Data will be presented in text and tables as means and 95% confidence intervals (CI) unless otherwise stated. Because of randomisation, we did not undertake analysis of baseline equivalence, since the null hypothesis must be true and any differences due to chance . Only participants who completed follow-up testing were included in analysis (i.e. per protocol analysis). The effect of the energy management intervention on main and secondary outcomes will be examined using two-way mixed-model ANOVA with condition (intervention or control) as the between-subjects factor and time (pre- and post-intervention) as a within subjects' factor. Alpha level will be reported as exact p values and not described dichotomously as 'significant' or otherwise as recommended by the American Statistical Association . We will express effect sizes from the ANOVA as partial eta-squared ( $\eta^2p$ ), with values of 0.01, 0.06, and 0.14 interpreted as small, moderate, and large, respectively . For categorical data, (DSQ-PEM questions 6-10) we will use McNemar's Test for paired samples (pre- to post- intervention), or Chi squared test for between group effects (intervention vs. control).

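### The protocol names two different sets of stratification factors and fixes an ANOVA that contains neither, so the primary test may be mildly conservative

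*Protocol*

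**What the plan says.** The protocol describes allocation in three places.

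- **Study implementation, subsection Protocol:** a third-party service "randomised participants into intervention or control groups stratified by age and sex".
- **Study procedure:** the same service placed participants in "intervention or control arms of the trial balanced for gender".
- **Randomisation:** "Participants will be randomised to one of the two trial arms using 1:1 allocation ratio", through a web-based system. No factor is named.

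None of the three gives age bands or the method of restriction (blocks, minimisation or other).

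Statistical methods fixes the analysis of main and secondary outcomes as a "two-way mixed-model ANOVA with condition (intervention or control) as the between-subjects factor" and time, before and after the intervention, as the within-subjects factor. It lists no age, sex or stratum term. Sample size and statistical power identifies the interaction as the test for which the trial was powered.

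**The concern.** The implementation section and Study procedure describe the same allocation by the same service, but they differ on whether age was a factor. An analyst who wants the model to follow the design cannot tell from the protocol which factors belong in it.

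The model itself contains none of them. Stratified allocation removes chance imbalance on the strata, so the true variance of the arm comparison is smaller. An analysis without the strata does not see this: it leaves their contribution in the residual and reports a standard error based on the larger variance. Where the strata predict the quantity being tested, confidence intervals are then too wide and p-values too large. This matters for reporting, because the protocol presents 95% intervals and exact p-values rather than a yes/no significance call.

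**Working it through.** **Inputs from the protocol.** Alpha 0.05, power 0.90, f = 0.25 (d = 0.5), two groups, two time points, interaction test, total N = 170 (Sample size and statistical power). Allocation descriptions and model as set out above.

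**Input not in the protocol.** R², the share of the variance of *change* in DSQ-PEM explained by the strata. The assumed range is 0 to 0.20.

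**Step 1: the plan's own figure.** Noncentral F with df 1 and N − 2 and noncentrality N × f². At N = 170 this is 170 × 0.0625 = 10.625, and power is 0.8999. The first N at or above 0.90 is 171, so the stated 170 reproduces to within rounding. The point below does not alter it.

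**Step 2: which variance matters.** With two time points, the condition by time interaction is the between-arm comparison of (post − pre). An age or sex effect that is the same at both times drops out of that difference. Only an effect on the change remains in the residual.

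**Step 3: size, large-sample normal approximation under stratified allocation.**

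- Reported SE / true SE = 1/√(1 − R²)
- True type I error of the unadjusted test = 2 × [1 − Φ(1.96/√(1 − R²))]
- Power at N = 170, with δ = 0.5 × √(170/4) = 3.260: unadjusted Φ((δ − 1.96)/√(1 − R²)); adjusted Φ(δ/√(1 − R²) − 1.96)
- N for 90% power relative to 170: unadjusted [(1.96 + 1.2816√(1 − R²))/3.2415]²; adjusted 1 − R²

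| Assumed R² of change | SE too large by | True type I error | Power unadjusted / adjusted | N unadjusted / adjusted | Extra N if unadjusted |
|---|---|---|---|---|---|
| 0 | 0% | 0.050 | 0.903 / 0.903 | 170 / 170 | 0% |
| 0.05 | 2.6% | 0.044 | 0.909 / 0.917 | 167 / 162 | 3% |
| 0.10 | 5.4% | 0.039 | 0.915 / 0.930 | 163 / 153 | 7% |
| 0.20 | 11.8% | 0.028 | 0.927 / 0.954 | 156 / 136 | 15% |

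**Step 4: simulation check under the null.** N = 170 and 6,000 runs. The assumptions are permuted blocks of 4 within sex by two-level age strata, 22% men, and between- and within-person SDs of 17.7 each, which give a total SD of √2 × 17.7 = 25.0.

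| Strata shift | Mean unadjusted SE | Empirical SD of estimate | Rejection rate |
|---|---|---|---|
| Level by 20 points, change by 0 | 3.84 | 3.83 | 4.8% |
| Change by 10 points | 3.96 | 3.81 | 4.2% |
| Change by 20 points | 4.32 | 3.87 | 2.9% |

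In the last scenario, adding stratum terms to the change-score model brought the mean SE to 3.84 and the rejection rate to 5.0%. The first row confirms Step 2: a large effect on level causes no inflation.

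**The case against.** The strongest reply is that the practical harm is small and in the safe direction. The estimate is unbiased, the test errs towards too few rejections, and at N = 170 the unadjusted test keeps at least the planned 0.90 power, to rounding, across the assumed range. The protocol gives no R², and 0.20 for change is an upper end that nothing in it supports. All of this stands and limits the weight of the point. It does not remove it. The table of participants who completed the study shows 77 + 84 = 161; at that number the plan's own calculation gives power 0.884, so precision is not in surplus.

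A second reply is that covariate lists are commonly left to a statistical analysis plan. Here the protocol itself fixes the model, and the conflict over age lies within the protocol.

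Three stronger readings are tempting, and the document does not support them.

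- *That there are three incompatible schemes.* The Randomisation section is silent on factors and contradicts neither of the others. The other two agree on sex or gender; only age is in conflict.
- *That standard errors are inflated whenever age or sex is related to DSQ-PEM.* For the planned interaction this fails, because a stable effect on level cancels. The factors must predict change.
- *That adjustment would save 5%, 11% or 25% of the sample,* from 1/(1 − R²) − 1. That is the gain under simple randomisation. Under stratified allocation the unadjusted estimate already has the smaller true variance, and only its reported SE is too large. The figures for equal 90% power are 3%, 7% and 15%.

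**Conclusion.** The conflict between the two descriptions, and the absence of any stratification factor from the fixed model, are plain on the page and need correcting whatever the numerical effect.

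The statistical consequence is conditional on two things: that allocation really was stratified, and that age or sex predicts change in DSQ-PEM. If both hold, the interaction test is mildly conservative, with a standard error 2.6% to 11.8% too large for an assumed R² of 0.05 to 0.20. If the strata predict level only, there is no effect on this test. If allocation was simple 1:1, the unadjusted test is valid and adjustment only adds precision. A reader might infer bias or an increased risk of a false-positive result; neither follows in any of these cases. The stated sample size is unaffected.

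**What to change.** 1. State one scheme, as actually configured in the randomisation service, with its factors, age bands and method of restriction. Use it consistently in the implementation section, Randomisation and Study procedure.
2. Include those factors in the continuous-outcome models in a form that reaches the arm comparison of change. Either add factor by time terms to the mixed ANOVA, or use an ANCOVA of the 6-month value on baseline, arm and the stratification factors (age and sex, if that was the scheme). Main-effect terms alone would leave the two-time-point interaction test essentially unchanged.

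The cost is one reconciled description and a slightly longer model. Age and gender are already tabulated for participants who completed the study. The chi-squared and McNemar tests planned for the categorical DSQ-PEM items take no covariates and are not covered by this change.

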## Activity allowance

Following enrolment, participants were set an initial activity allowance to avoid accumulating more than 30 minutes with a heart rate above 60% of their age-predicted HRmax. This limit was designed to be iterative and revised in response to how well they managed their pacing and whether or not they experienced bouts of PEM. When participants reported PEM, an automatic review of their activity data would be triggered. The review examined their activity data over the preceding three days (since PEM may be delayed by several days). If participants had exceeded their activity allowance in those three days, this would be noted as ‘poor pacing’, and no changes would be made to the activity allowance. If participants had exceeded their activity allowance in any one of the three previous days, that was considered an ‘inappropriate allowance, and the activity allowance was reduced using a stepwise algorithm. Where participants did not log bouts of PEM for three continuous weeks, the activity allowance would be increased again in a stepwise algorithm. It is important to note that during enrolment, care was taken to be clear to participants that the activity allowance was a reference point against which participants could gauge their current activity. It was not intended as a target to be met, and at no point would participants be urged to do additional activity to ‘meet their allowance.

In some cases, HR was an inappropriate metric for measuring pacing. Participants may have cardiac autonomic issues resulting in high or unstable resting heart rates, which interfere with the link between current heart rate and activity. Alternatively, participants may experience several recurring bouts of PEM, which, if the activity allowance were continually revised, would result in an allowance too low for participants to feasibly stay within. In these cases, participants were switched to a step-count activity allowance, also using the data from the same tracker.

The initial step-activity-allowance was determined by finding the highest number of steps per day that was not followed by PEM in the following three days. After that, the process of altering the step-activity-allowance was similar. When participants registered PEM, the step-activity limit would be reduced only if they had stayed within their current limit for the previous three days. Where no PEM was registered for three continuous weeks, the step-activity-limit would be revised upwards.

## Pace Me App Display

The home screen of the PaceME app included a live display of participants’ pacing progress for that day. For those using a heart-rate-based activity allowance, the display showed the heart rate they should stay below, how many minutes they had accumulated above that heart rate, along with an indicator of how much of their activity allowance they had ‘used’ that day (e.g. if their limit was no more than 30 minutes above 120 bpm, and they had accumulated 15 minutes, the indicator would show 50%;). For those who had been switched to a step count activity allowance, a similar display of the day’s step count was displayed instead.

In addition, a separate screen displayed additional information, including a series of indicators. These included a set of emoji indicators showing how well they had paced over the preceding three days to remind them how well they had managed to pace recently. In addition, there were a series of graphs showing (a) when on the current day they had spent most time above their activity allowance, (b) when on average over the last week had they accumulated the most activity (i.e. most active hours of

the day to be aware of ) (c) when in the current day they had spent most time resting. The aims of these indicators were to help participants understand the times of day when they were most likely to be overly active and when they tended to get the most rest. In addition, we were cognizant of the risk of overwhelming participants with information, and as such, these additional screens were hidden and revealed when tapping a specific icon.

## Messaging

The intervention also provided messages to alert participants as their accumulated time above their activity allowance increased. Our prior PPI work indicated that a concern of participants was receiving too many notifications, which also can reduce participant engagement with an intervention. As a result, our intervention would send a maximum of three pacing notifications per day. In addition, because we had turned off all Fitbit notifications, the PaceME app also took over alerting participants if the tracker battery was low or had not synced with the Fitbit servers for more than 2 hours. As a result, participants could receive between zero and five daily alert notifications.

Pacing alerts were personalised to each participant's current activity allowance, and where interactive notifications were triggered by our activity server when participants had reached 50%, 75% and 100% of their activity allowance. The alert comprised of a standard phone notification with the PaceME logo and a text header '{Name} has reached {xx%} of your activity allowance' (where {Name} and {xx%} represent the participant's first name and the relevant level of their activity allowance that had been reached). When tapped on the PaceMe app opened and displayed an infographic containing a pacing support message. The support messages were provided as part of a separate project to crowd-source pacing advice messages from people with ME/CFS who had used activity pacing for a long time. We curated these responses and collated them into relevant infographics to use as messaging support.

Sync notifications were not interactive, and when tapped they opened the Fitbit app to trigger syncing between the data stored on the tracker and the Fitbit servers. Similarly, the low-battery notifications were not interactive, and a simple notification with a logo and a message that their tracker was battery charge was below 20%.

Data flow for energy management support. A: Participants provided with a tracker and all notifications to increase activity turned off. B: The tracker's own app tracks and stores activity metrics (HR, Steps etc), C: Our server pulls the data from Fitbit every 3 minutes and re-processes to be useful for individualised energy management targets, D: Processed data is streamed to Pace Me app, E: participants log bouts of post-exertional malaise (PEM) which is used to determine the current energy management limit, F: Alerts are sent to the app as participants increase the time spent above their limit.

## DATA PIPELINE VISUALISATION

[figure not shown]

Supplementary figure displaying the data pipeline from the wearable device to the FitBit app, which had notifications hidden from participants (A), then was transferred to the FitBit cloud (B), which we pulled down onto our server (C). This data then updated the participants app with near-live pacing information (D), and then if participants reported PEM events (E), this influenced our pacing algorithm. Finally, the data were used to send pacing alerts when participants reached certain thresholds.

## PARTICIPANT DEMOGRAPHICS

Supplementary table displaying participant characteristics of those who completed the study.

|              | Control (n=77)         | Intervention (n=84)    |
|--------------|------------------------|------------------------|
|              | Mean (95% CI)          | Mean (95% CI)          |
| Age (years)  | 47 (45-50)             | 45 (43-48)             |
| Gender (M/F) | 60 F (78%), 17 M (22%) | 66 F (79%), 18 M (21%) |

## EMPLOYMENT STATUS AT BASELINE

[figure not shown][figure not shown]

Supplementary figure displaying the employment status of all participants at baseline. Not all participants completed the questionnaire, thus why the total n is not 125 per group.

## DAYS WITHOUT PEM

[figure not shown]

Supplementary figure displaying the mean number of days per month that participants did not report a PEM event. Data are mean and 95% confidence intervals.

## BACKGROUND

People with long COVID report 'push-crash' cycles, with a disproportionate worsening of

symptoms in response to activity, similar to post-exertional malaise (PEM) reported by patients with chronic fatigue syndrome. These PEM-like symptoms increase the overall symptom load, reduce each individual's quality of life, and make recovery harder.

Adaptive pacing has emerged as a common strategy to self-manage PEM-like symptoms. Our systematic reviews suggest adaptive pacing is effective in improving some symptoms in people with ME/CFS. However, recent work endorsed by our long COVID PPI group indicates that implementing adaptive pacing is often problematic for those attempting to self-manage. Difficulties include accurately estimating concepts such as energy availability and predicted energy use and identifying and tracking a suitable threshold to limit activity. Combining these requirements to plan daily activities, often hour by-hour, can be highly challenging, particularly when symptoms include impaired cognition.

This project aims to determine if combining continuous activity tracking with a just-in-time adaptive intervention (JITAI) can address these limitations. JITAIs provide information to participants at a time and context where they can act upon it. Widely used in behaviour change research, JITAIs are yet to be applied to adaptive pacing. Using a randomised control study design, we will allocate 250 participants to receive either JITAI supported adaptive pacing or usual care. Our primary outcome is PEM using the De Paul Symptom Questionnaire (DSQ)-PEM at baseline and 6 months.

